## 6.3 Safety

In this study, patient safety will take the highest priority in the routine assessment and management of study patients. Safety will be evaluated using adverse reactions as graded by standard NIAID/ACTG toxicity tables. All Grade IV adverse events will be reported to the Institutional Review Boards at respective institutions (Section 11.3), the study sponsor, and the Data Safety and Monitoring Board (Section 11.4).

### **6.3.1 Toxicity and Serious Adverse Experiences**

Serious adverse experiences will be identified through 1) active case finding using a standard protocol for clinical evaluation and laboratory investigation and 2) passive case finding when patients seek medical care in a sick visit. Serious adverse experiences (SAE) (21 CFR 314.80) are any adverse experience occurring at any dose that results in: death, a life-threatening adverse drug experience (as defined by Grade 4 Adverse Event), inpatient hospitalization or prolongation of an existing hospitalization, a persistent or significant disability or incapacity, or a congenital anomaly or birth defect. Other events not resulting in death, that are not life-threatening or that do not require hospitalization may be considered to be SAE when, based on appropriate medical judgment, they jeopardize the patient and may required medical or surgical intervention to prevent one of the above outcomes.

Suspected abacavir-related HSR will be reportable through a separate form designed to record information on all suspected cases. If the syndrome is confirmed or meets the criteria as a SAE, then a separate SAE report will be completed as described below. While not defined by U.S. regulations as a serious adverse experience, pregnancy will be reported to the study sponsor as an SAE using the SAE reporting form, thus allowing collection and tracking of this information in a systematic manner.Reporting of pregnancy in this way ensures proper referral to antenatal clinics and accordance of contraindicated medication.

#### **6.3.1.1 Procedures for Reporting Serious Adverse Experiences**

All serious adverse experiences as defined in Section 6.3, occurring in study subjects during the course of the study must be reported promptly to the Principal Investigator, the Data Coordinating Center at UCSF, the TB Research Unit Coordinating Center at CWRU and the Study Sponsor (DAIDS) at the following address:

The DAIDS Regulatory Compliance Center (RCC)/Safety Office,

e-mail address: [contact],

[contact],

[contact].

The study site physician also is responsible for reporting any SAE arising during the conduct of the study to the local IRB.

Requirements for adverse experiences requiring reporting are listed and summarized in the following flow diagram:

**Figure 3. Adverse Experiences that Must Be Reported**

**Does this finding represent a change from baseline?**



**YES NO** *No report is required*



**Is the finding *SERIOUS*?** (Did one of the following events result?)

- Death
- Life-threatening adverse drug experience, i.e., Grade 4 adverse event
- Required hospitalization or prolonged and ongoing hospitalization
- Persistent or significant disability or incapacity
- Congenital anomaly or birth defect.
- Jeopardized the patient or subject and required medical or surgical intervention to prevent one of the outcomes listed above



**Yes No** *No report is required*



***Report on Serious Adverse Experience form within one business day of learning of event***

#### **6.3.1.2 Specific Adverse Reactions**

Both antituberculosis therapy and antiretroviral therapy are associated with well-described adverse reactions. These adverse reactions will represent study outcomes and are specifically defined below. Management of these conditions will be described in Clinical Management (Section 8.0).

##### 6.3.1.2.1 Hypersensitivity Reaction (HSR) associated with Abacavir (ABC)

In clinical studies, approximately 3%-5% of patients receiving ABC develop an HSR that in rare cases has proved fatal. HSR is characterized by the appearance of symptoms indicating multi-organ/body system involvement. Symptoms usually appear within the first 6 weeks of starting treatment with ABC (median time to onset is 11 days), but may occur at any time while on therapy.

This section describes the diagnostic criteria that will be operationalized in the study. The clinical management of the syndrome is described under Clinical Management (Section 8.1.2.2.3). In this protocol we will distinguish the clinical diagnosis made at the time of evaluation from the final classification of a suspected HSR that will be used in the analysis. The clinical diagnosis will be made by the study team on-site using information available at the time of the evaluation. For the analysis, the Clinical Review Committee will examine all available data including the clinical course after ABC is withdrawn. This later classification will be used in the analysis of the study.

Clinical Diagnosis of ABC HSR

The diagnosis of HSR will be suspected when a patient receiving ABC presents to a routine or sick visit with a combination of fever, rash, gastrointestinal symptoms, worsening respiratory symptoms, neurologic symptoms. Although there is no diagnostic test available to confirm the clinical diagnosis of HSR, a routine medical evaluation will be performed including vital signs and physical examination looking for clinical characteristics of HSR. Standard laboratory evaluation will include CBC with differential count, serum chemistries, creatinine, and liver function tests. If liver enzymes are abnormal, then viral serologies for hepatitis A and B will be drawn.

Because the signs and symptoms of HSR are non-specific, and may be confused with side effects of rifampin, other HIV conditions, or paradoxical reactions, the evaluations of these patients will be as extensive as possible to allow for accurate diagnosis at the time of the event and proper classification for analysis.

HSR is defined as a clinical syndrome with findings from two or more of the following groups of signs or symptoms occurring simultaneously in a patient receiving ABC:

- Fever > 38°C
- Rash
- One or more gastrointestinal symptoms: nausea, vomiting, abdominal pain, diarrhea
- One or more respiratory symptoms not directly referable to active TB: dyspnea, non-productive cough, sore throat
- One or more musculoskeletal symptoms: myalgia, arthralgia
- One or more neurologic symptoms: headache, paresthesias

All suspected cases of HSR will be reviewed with on-site investigator during the clinic visit in which the diagnosis is suspected. A course of diagnosis and management will be delineated at that time. A decision tree to evaluate the occurrence of an abacavir-related HSR is summarized in the following flow diagram:

**Figure 4. Diagnosis of Abacavir-related HSR**

**Does the patient present with two or more of the following symptoms?**

- Fever > 38°C
- Rash
- One or more gastrointestinal symptoms (nausea, vomiting, abdominal pain, diarrhea) occurring while treating with Trizivir
- One or more respiratory symptoms not directly referable to tuberculosis: dyspnea, non-productive cough, sore throat
- One or more systemic musculoskeletal symptoms: myalgia, arthralgia (involving multiple joints)
- One or more neurologic symptoms: severe headache, paresthesias not attributable to INH
- Side effects of other antiretroviral medications.



**YES NO** *HSR not suspected*



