##### 8.1.2.2.3 Adverse Experiences to Abacavir (ABC)

ABC Hypersensitivity Reactions (HSRs) - *Background*

In clinical studies, approximately 3%-5% of patients receiving ABC develop an HSR that in rare cases has proved fatal. HSR is characterized by the appearance of symptoms indicating multiorgan/body system involvement. Symptoms usually appear within the first 6 weeks of starting treatment with ABC (median time to onset is 11 days), but may occur at any time while on therapy, and most often include fever, rash, gastrointestinal symptoms (nausea, vomiting, diarrhea, or abdominal pain), respiratory symptoms (dyspnea, sore throat, cough), and lethargy or malaise. Other signs and symptoms may include musculoskeletal symptoms (myalgia, rarely myolysis, arthralgia), headache, paresthesia, and edema. Respiratory tract symptoms (dyspnea, sore throat, cough) have been observed in approximately 20% of subjects who experience HSR.

The diagnosis of hypersensitivity to ABC remains a clinical diagnosis. There is no pathognomonic clinical sign or laboratory finding that renders the diagnosis. The key feature is that HSR is a multi-organ system reaction. Some patients with HSRs were initially thought to have respiratory tract disease (pneumonia, bronchitis, pharyngitis) or a flu-like illness. The multisystem nature of the HSR has led to misdiagnosis of the HSR as an intercurrent medical illness or as being related to another medication. HSR also has been unrecognized when it presents with less common symptoms or as a single symptom.

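### The on-site definition of suspected abacavir hypersensitivity in 6.3.1.2.1 and the Figure 4 said to summarize it disagree in both directions

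*Protocol*

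**What the plan says.** Section 6.3.1.2.1 separates two steps: a clinical diagnosis made on site with the information then available, and a later classification by the Clinical Review Committee, which is the one analysed.

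For the on-site step, which concerns patients on abacavir, the text says "HSR is defined as a clinical syndrome with findings from two or more of the following groups of signs or symptoms occurring simultaneously". Six groups are then given: fever, rash, gastrointestinal, respiratory, musculoskeletal and neurologic. The last two read "One or more musculoskeletal symptoms: myalgia, arthralgia" and "One or more neurologic symptoms: headache, paresthesias", without qualifiers. A sentence earlier in the same subsection says HSR is suspected when a patient presents "with a combination of fever, rash, gastrointestinal symptoms, worsening respiratory symptoms, neurologic symptoms"; it does not name the musculoskeletal group.

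The text then introduces Figure 4: "A decision tree to evaluate the occurrence of an abacavir-related HSR is summarized in the following flow diagram". The figure asks whether two or more listed items are present. Its neurologic item is "One or more neurologic symptoms: severe headache, paresthesias not attributable to INH". Its musculoskeletal item is restricted to systemic symptoms, with arthralgia in multiple joints. A seventh item, side effects of other antiretroviral drugs, stands in the list to be counted. The NO branch ends at HSR not being suspected. The YES branch leads to presentation to the on-site clinician before the patient leaves, a decision on abacavir, the HSR Evaluation and Follow-up Protocol, and a report within one business day.

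**The concern.** A summary figure should return the same answer as the definition it summarizes, and this one does not. Section 8.1.2.2.3 makes the management of abacavir depend on a diagnosis of suspected HSR under the standard definitions, but two definitions are in force. Staff working from the text and staff working from the figure can send the same patient down different paths at the same visit.

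This is a safety matter by the protocol's own account: 8.1.2.2.3 says that misattributed or delayed diagnosis has led to abacavir being continued or reintroduced, with more severe reactions or death. The number of suspected cases reported on the HSR form also depends on which list was used.

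**Working it through.** The plan states no figure to reproduce, so the check compares the lists.

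| Item | 6.3.1.2.1 text (on site) | Figure 4 (on site) | Final classification |
| --- | --- | --- | --- |
| Threshold | two or more groups, simultaneous | two or more, simultaneity not stated | two or more groups, simultaneous |
| Fever, rash, gastrointestinal, respiratory | counted | counted | counted |
| Myalgia, arthralgia | any | systemic; arthralgia in multiple joints | as Figure 4 |
| Headache | any | severe only | as Figure 4 |
| Paresthesias | any | only if not attributable to INH | as Figure 4 |
| Side effects of other antiretrovirals | absent | counted | absent |

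Figure 4 and the final classification tie the gastrointestinal item to treatment with Trizivir, while the text refers to a patient receiving abacavir. The two are treated as equivalent here.

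**Group pairs.** Six groups give 6×5/2 = 15 pairs. The four groups counted alike give 4×3/2 = 6 pairs on which text and figure must agree. The remaining 15 − 6 = 9 pairs involve the musculoskeletal or neurologic group and can be classified differently.

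**Two-finding presentations.** Take 12 findings that the lists name or qualify: fever; rash; gastrointestinal; respiratory not referable to TB; single-joint arthralgia; multi-joint arthralgia; non-severe headache; severe headache; INH-attributable paresthesias; other paresthesias; malaise; side effect of another antiretroviral. They give 12×11/2 = 66 pairs.

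- Text met, Figure 4 not met:
  - any of the four common groups with single-joint arthralgia, non-severe headache or INH-attributable paresthesias: 4×3 = 12
  - single-joint arthralgia with any of the four neurologic findings: 4
  - multi-joint arthralgia with non-severe headache or INH-attributable paresthesias: 2
  - total: 12 + 4 + 2 = 18
- Figure 4 met, text not met: the seventh item with fever, rash, gastrointestinal, respiratory, multi-joint arthralgia, severe headache or other paresthesias: 7.

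The enumeration takes both findings as present together, so it does not capture the missing simultaneity condition.

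**Effect on the analysed count.** A patient whose only findings are fever and non-severe headache fails the final classification too, whichever bedside list was used. A patient admitted only through the seventh item also fails it on those findings. The bedside list can change the final count only where the illness evolves after the visit and one list, but not the other, put the patient on close follow-up.

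**The case against.** The best defence is that the mismatch has little reach. Much of this stands, and it rules out several stronger readings.

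- **A shift in the analysed HSR rate.** At the protocol's 3–5%, 0.03×175 = 5.3 to 0.05×175 = 8.8 reactions are expected, so one case is 1/8.8 = 11% to 1/5.3 = 19% of the total. A reader might take this as the effect of the conflict. It is true of any single case, the share of cases affected is not given, and the final classification already carries Figure 4's qualifiers.
- **A third trigger list in 8.1.2.2.3.** That section mentions "respiratory symptoms (dyspnea, sore throat, cough), and lethargy or malaise" and warns that "HSR also has been unrecognized when it presents with less common symptoms or as a single symptom". But this is headed as background, and the section refers back to 6.3.1.2.1 for the diagnosis. It is a differing description, not a competing rule. A two-group threshold set alongside it is a clinical choice.
- **A NO in Figure 4 closes every route.** It does not. Section 8.1.2.2.3 asks that HSR be considered even when another diagnosis seems likely, and flags fever as a possible herald. Section 8.1.2.2.6 calls for evaluation for abacavir HSR in a patient with rash. Adverse-event recording and SAE reporting continue regardless, and the Committee reviews all Table 6 outcomes, which include grade III/IV reactions.
- **The qualifiers will often bite because everyone takes TB drugs.** The protocol gives INH neuropathy as 0.2–2%, with pyridoxine for all patients, and no Figure 4 qualifier refers to pyrazinamide.

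The seventh item may have been meant as an alternative explanation to exclude. As printed, it is in the list to be counted.

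What the defence does not remove is the disagreement itself. The safeguards in 8.1.2.2.3 mostly presuppose that HSR is already suspected: the fever paragraph, for example, places a patient on the follow-up protocol only if it is.

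**Conclusion.** The point holds as an internal contradiction between the 6.3.1.2.1 text and Figure 4, running both ways: 18 of 66 constructed two-finding presentations meet the text only, 7 meet the figure only, and 9 of 15 group pairs can be affected. These counts rest on reading the lists literally and on the 12 findings chosen. They are not expected patient frequencies.

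An intended difference is hard to defend. The figure is introduced as a summary, and its musculoskeletal and neurologic wording is that of the final classification, which the same section says is distinct from the on-site diagnosis.

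The consequence is operational: which patients get same-visit review, an abacavir decision, the follow-up protocol and an HSR report. The effect on the analysed HSR count is limited and cannot be quantified from the documents. Correction is advisable because the figure gates a safety pathway. Which list is clinically right is not judged here.

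**What to change.** Reconcile the 6.3.1.2.1 text, including its opening sentence that omits the musculoskeletal group, with Figure 4 and the HSR reporting form, so that one bedside list is used throughout. Within that list, settle whether simultaneity is required and whether side effects of other antiretrovirals are counted, excluded or removed. State whether the bedside list is meant to differ from the final classification and, if so, where. Check the result for consistency with the background description in 8.1.2.2.3. The investigators decide the clinical content, including which qualifiers apply at which step.

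The cost is wording in one figure and the related text, the HSR form, and a notice to site staff. The number of suspected cases to evaluate may rise or fall slightly, depending on the list adopted.

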**AND**

Exclusion of the following conditions as a cause of the symptom complex:

- Chemical (especially rifampin) or viral hepatitis
- Gout, arthritis or arthralgias caused by pyrazinamide
- Exacerbation of underlying tuberculosis
- Immune reconstitution syndrome (IRIS) to TB (paradoxical reaction)
- HIV-related condition such as cryptococcal meningitis, oral thrush, esophageal candidiasis, cryptosporidiosis/microsporidiosis, etc.

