**AND**

Resolution of symptoms with the discontinuation of ABC. Resolution of symptoms within 48 to 72 hours will constitute the strongest evidence for HSR

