##### 8.1.2.2.1 Nausea (with or without vomiting)

Nausea following initiation of therapy with antiretroviral medications usually subsides or resolves during the first few weeks of treatment. With the onset of Grade >1 nausea, patients will be advised to take study drugs with food. With Grade >1 nausea, subjects may be treated as needed with antiemetics given orally or by suppository.

If the nausea is considered related to ZDV and is treatment limiting in the opinion of the site investigator, allowable drug substitution should be considered.

If nausea persists despite food and antiemetics or increases in severity, interrupt drug therapy. Once nausea resolves, therapy must be resumed using the full doses of study drugs, with the exception of the ZDV dose reduced to 200 mg BID. The dose will be increased as tolerated thereafter. If intolerable nausea recurs following resumption of therapy, protocol-allowable drug substitution(s) should be considered.

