If the clinical team makes the diagnosis of suspected HSR according to the standard definitions, then ABC will be held and discontinued when the diagnosis is confirmed by the resolution of symptoms. Patients with suspected HSR will be placed on the ‘ABC HSR Evaluation and Follow-up Protocol’. This protocol will involve complete initial diagnostic evaluation as described above, close follow-up with detailed evaluations by study physicians until all symptoms resolve or until an alternative diagnosis is established. Each patient placed on this protocol will be reviewed by experienced study clinicians and discussed with the senior study investigator at the point of patient contact. The information collected during this follow-up period will be recorded on a standard clinical report form for later review and classification.

In some cases of suspected HSR, the signs and symptoms consistent with ABC HSR may be mild or attributed to an intercurrent medical illness. In these cases, on-site physicians may decide to continue the ABC while monitoring signs and symptoms closely for any further development of ABC HSR. This decision will only be made after consulting senior investigators on the study at the point of patient contact. If signs or symptoms evolve, or HSR cannot be ruled out, ABC will be discontinued, even when other diagnoses are possible or likely (e.g., respiratory tract infections, gastroenteritis, or adverse events related to another drug).

In cases where the diagnosis of ABC HSR is strongly suspected, the patient will be instructed to hold all antiretroviral medications including ABC pending further evaluation. If signs and symptoms of ABC HSR resolve after discontinuing the medication, then the clinical diagnosis will be established, and ABC will be discontinued. The patient will be started on a protocol-allowable substitution regimen. The patient will be instructed to return unused ABC medication or combinations containing ABC to the clinic. The patient will be advised that they should never take ABC again, as life-threatening HSR may occur.

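### Figure 4 counts other antiretrovirals' side effects as a symptom of abacavir hypersensitivity, and the final classification does not exclude them as a cause

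*Protocol*

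**What the plan says.** Section 6.3.1.2.1 describes abacavir HSR three times.

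- **Clinical definition (text).** "HSR is defined as a clinical syndrome with findings from two or more of the following groups of signs or symptoms occurring simultaneously". Six groups follow: fever, rash, gastrointestinal, respiratory, musculoskeletal and neurologic.
- **Figure 4**, presented as a summary of the clinical evaluation. It opens with "Does the patient present with two or more of the following symptoms", gives the same six groups, and adds a seventh line: "Side effects of other antiretroviral medications". A yes leads to suspected HSR.
- **Final diagnosis for analysis.** Two or more of the six groups, then "Exclusion of the following conditions as a cause of the symptom complex", then "Resolution of symptoms with the discontinuation of ABC". The exclusions are chemical or viral hepatitis, pyrazinamide joint effects, worsening tuberculosis, immune reconstitution syndrome and HIV-related conditions.

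The same section says that the Clinical Review Committee makes the final classification from all available data, including the course after withdrawal, and that this classification is the one analysed. Section 6.3.1.2 makes these reactions study outcomes. Under Section 8.1.2.2.3, where HSR is strongly suspected, "the patient will be instructed to hold all antiretroviral medications including ABC pending further evaluation".

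**The concern.** A side effect of a companion drug is a competing explanation for a symptom. Counting it toward the threshold makes HSR look more likely when evidence for another cause is present. It would fit naturally among the final exclusions, but it is absent there. Every patient on Trizivir takes zidovudine and lamivudine with abacavir, so this is the competing cause to which every Trizivir-treated patient is exposed.

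Two things are at stake. At the bedside, the text and its own flow diagram give different answers for the same patient. In the analysis, the written criteria for a defined safety outcome contain nothing that removes a companion-drug reaction spanning two symptom groups. Such a reaction would be reported as abacavir HSR.

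**Working it through.** The protocol gives no figure to reproduce here. The check sets the rules side by side and runs two hypothetical patients through them.

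**The lists**

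| Rule | Symptom groups | Side effects of other antiretrovirals | Neurologic group |
|---|---|---|---|
| Clinical text | 6 | not mentioned | "One or more neurologic symptoms: headache, paresthesias" |
| Figure 4 | 6, plus the extra line | counted toward two | headache must be severe; paresthesia not due to isoniazid |
| Final diagnosis | 6 | neither counted nor excluded | as in Figure 4 |

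The extra line is in 1 of 3 symptom lists and in 0 of 5 final exclusions. The musculoskeletal group differs too: the clinical text accepts any myalgia or arthralgia, while Figure 4 and the final diagnosis require systemic symptoms, with arthralgia in multiple joints.

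**Patient A: nausea attributed to zidovudine, nothing else.** Section 8.1.2.2.1 anticipates this: "Nausea following initiation of therapy with antiretroviral medications usually subsides or resolves during the first few weeks of treatment". It goes on to deal with nausea considered related to zidovudine.

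- Clinical text: 1 group, below 2, so not HSR.
- Figure 4, read literally: gastrointestinal (1) + extra line (1) = 2, so suspected HSR.
- Final diagnosis: 1 group, below 2, so not HSR.

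**Patient B: nausea and severe headache from a companion drug; all antiretrovirals held; both settle.** Section 1.1.2 attributes gastrointestinal and central nervous system effects to antiretrovirals in general. That the second includes headache is an assumption.

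- Symptom criterion: gastrointestinal + neurologic = 2, met.
- Exclusions: none of the five applies. Only an antiretroviral hepatitis could fall under the chemical hepatitis entry.
- Resolution criterion: abacavir was stopped and symptoms resolved, so it is met in form. The companion drugs were stopped at the same time, so resolution does not identify the drug.
- Result: all three written parts are met.

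**Scale.** The punctuated arm has 175 patients (Table 4), and Section 6.3.1.2.1 gives an HSR rate of 3% to 5%.

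- Expected true cases: 0.03 × 175 = 5.25 and 0.05 × 175 = 8.75, so about 5 to 9.
- One misattributed case: 1/175 = 0.57 percentage points.
- Relative to the expected count: 1/8.75 = 11% to 1/5.25 = 19% per case.

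How many patients resemble Patient B cannot be derived from the protocol.

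**The case against.** **Figure 4 does not decide the analysis.** This stands. It yields only a suspected case, the extra line is not in the final definition, and Patient A fails there.

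**The committee has the information it needs.** This stands in large part. It sees the course after withdrawal, and the substitute regimen in Section 5.2.1.4 is efavirenz with lamivudine/zidovudine, so recurrence on zidovudine without abacavir would be visible. Early resolution, within 48 to 72 hours, is named as the strongest evidence. But no written criterion tells the committee to use recurrence, and early resolution does not identify the drug when all were stopped together.

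**The two-group example is thinly supported for zidovudine.** This also stands. The effects the protocol ties to zidovudine are nausea, anemia and neutropenia, which touch one of the six groups. The two-group case rests on the general statement in Section 1.1.2.

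**A sensitive bedside screen is deliberate.** Section 8.1.2.2.3 explains that mistaking HSR for something else has led to deaths. That supports broad suspicion. It does not explain listing a cause as a symptom, or why the figure and the text disagree.

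**The bedside consequence is limited.** A reader might infer that a yes in Figure 4 leads to permanent withdrawal of abacavir. The protocol does not say so: Figure 4 and Section 8.1.2.2.3 allow abacavir to continue when another cause is likely, and Section 8.1.4.2.3 allows a restart when the event is clearly ascribed elsewhere. However, Section 8.1.2.2.3 also stops abacavir when HSR cannot be ruled out, even if a reaction to another drug is likely.

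**Layout.** Figure 4 is a flow diagram seen here as running text, so the extra line could be a displaced fragment. Its absence from the exclusions would remain.

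**Conclusion.** The point holds in a limited form. Figure 4 contradicts the definition it summarises and can produce a suspected HSR from a single companion-drug symptom. Separately, the final classification does not name side effects of other antiretrovirals as an exclusion, and its resolution criterion cannot by itself separate the drugs when all were held. Companion-drug effects in two symptom groups can therefore meet the written analysis definition.

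A reader might go further and infer that zidovudine side effects will be classified as abacavir HSR and inflate its rate by some multiple. The documents do not support that: the counted line is dropped at the final step, two of six groups are still needed, the committee reviews all data, and the protocol gives no frequency for such reactions.

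The supportable size is per case: about 0.6 percentage points each, against about 5 to 9 expected cases. This assumes that all 175 punctuated-arm patients take abacavir, and it leaves out any exposure after the primary outcome. HSR has no line of its own in Table 6 and no dedicated between-arm test in Section 10.2.2.3, so the primary conclusion is not affected. The correction is still worth making, because the affected outcome is rare, safety-critical and defined by these written criteria.

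**What to change.** **Analysis classification (Section 6.3.1.2.1, final diagnosis).** Add side effects of other antiretrovirals to the excluded causes. Have the Clinical Review Committee record a case as indeterminate for attribution when all antiretrovirals were held and the later course does not separate the drugs. Report indeterminate cases alongside confirmed ones.

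**Bedside suspicion and handling.** The clinical definition, Figure 4 and the management text in Section 8.1.2.2.3 must be reconciled, including the differing headache, paresthesia and arthralgia wording. Which clinical rule should prevail is for the protocol team and is not proposed here.

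**Cost.** A wording change and an update to the HSR form, with no added visits or tests. The small downside is that some cases will be indeterminate.
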